### Sample size

The sample size is calculated using the two means comparison formula. Based on Afarwuah, the standard deviation is obtained at 0.95 [9]. The sample size calculation is performed using the 95% confidence level, 80% power, and an estimated difference in the weight-for-length Z-score and drop-out of 0.30 and 20%, respectively. Based on the formula and data used above for the minimal sample size, 540 subjects are required for this study. Considering the feasibility of subject and study implementation, 90 subjects per district are required: 30 subjects as a control group or arm 1, and 30 subjects each as intervention group 1 or 2 (arm 2 or 3). Thus, a minimum of 6 districts is needed to meet the minimum sample size required.

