### Outcome measures

Primary: Nutritional status of wasting children.

The measurement will be recorded through study completion, from baseline and at third, sixth, and ninth months. Anthropometry measurements will be based on the weight-for-length indicator (WHO Child Growth Standards).Secondary: PMT biscuit compliance.

The measurement will be recorded through study completion, at the first to third months after the start of treatment and then at the sixth and ninth months from the beginning of treatment.

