### Plan of data analysis and presentation

All data analysis will be performed using SPSS version 20. The data of the study subjects, both children characteristics and mother/caregiver characteristics, will be analysed to obtain the distribution frequencies and central tendencies as appropriate to the data scale. All subject characteristics of each arm will be analysed and compared with each other to assess their comparability at the beginning. No missing data are expected, and all loss to follow-up study participants will be excluded. The comparison of the weight-per-length score between groups and between times will be performed using ANOVA. The study subjects’ compliance to take biscuits will also be analysed and reported. The final dataset will be accessible to all authors without masking.

The research team is responsible to make annual and final reports to the Ministry of Health. The dissemination of the study results will be presented at the national nutritional meetings in the three regions. The scientific publications are the rights and responsibility of the research team.

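### The only primary analysis named is ANOVA, for an outcome measured four times on each child; the child term, the role of baseline and the deciding contrast are left open, and each reading has a weakness that one sentence would remove

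*Protocol article*

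**What the plan says.** Under Outcome measures, the primary outcome is nutritional status by weight-for-length, and "The measurement will be recorded through study completion, from baseline and at third, sixth, and ninth months". Each retained child therefore contributes four correlated scores.

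Under Plan of data analysis and presentation, the whole primary analysis is "The comparison of the weight-per-length score between groups and between times will be performed using ANOVA". Two neighbouring sentences bear on it: "All data analysis will be performed using SPSS version 20", and "No missing data are expected, and all loss to follow-up study participants will be excluded". The section names no type of ANOVA, child term, role for baseline, primary visit or deciding contrast.

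Under Sample size, "The sample size is calculated using the two means comparison formula". The inputs are a standard deviation ("the standard deviation is obtained at 0.95"), error rates ("performed using the 95% confidence level, 80% power") and "an estimated difference in the weight-for-length Z-score and drop-out of 0.30 and 20%, respectively". No within-child correlation appears.

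**The concern.** The sentence assigns one method to two comparisons. One of them, between times, is made within the same children by design. ANOVA without qualification assumes independent errors, and four scores from one child are not independent.

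If the scores were pooled, the error term would be wrong in both directions. The arm test would count each child four times, so its standard error would be too small. The arm-by-time test would keep stable differences between children in its error, so its standard error would be too large. One table could then show a false overall difference between arms and a false absence of differential improvement.

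Even where the error term is right, the sentence does not say whether baseline is an outcome or a covariate, or which F test or contrast answers the efficacy question. The choice could then be made after the data are seen, and the same section leaves the final dataset unmasked to all authors.

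**Working it through.** **Inputs.** From the protocol article: SD 0.95, difference 0.30, 5% level (two-sided assumed), 80% power, 20% drop-out, 540 children in three equal arms, four visits. Assumed: equal correlation rho between any two visits, at 0.3, 0.5 and 0.7, and no sub-district clustering.

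**The plan's own figure.** n per arm = 2 × [0.95 × (1.96 + 0.84) / 0.30]² = 157.4, so 158, or 474 for three arms. Allowing for 20% loss gives 158/0.8 = 198 per arm (594), or 158 × 1.2 = 190 per arm (570). Neither is 540. That is a separate matter; here I take 540/3 = 180 per arm, less 20% = 144. A single-visit comparison of two arms then has power Φ(0.30 / [0.95 × √(2/144)] − 1.96) = 76%.

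**Reading 1: all four scores pooled as independent.**
- Arm test: the true variance of an arm mean is 1 + 3·rho times what the model assumes. With 2 and 1,716 degrees of freedom the critical F is 3.00, so the null rejection rate is P(χ²₂ > 6.00 / (1 + 3·rho)).
- Arm-by-time test: the mean square is scaled by 1 − rho. For 0.30 in both biscuit arms at months 3, 6 and 9, the squared centred arm effects sum to 0.06 and the squared centred time pattern to 0.75. The non-centrality is 144 × 0.06 × 0.75 / [0.95² × (1 − rho)] = 10.3, 14.4 and 23.9.

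| rho | Arm test, true null rejected (nominal 5%) | Arm-by-time power, pooled | Arm-by-time power, child term |
|---|---|---|---|
| 0.3 | 21% | 36% | 65% |
| 0.5 | 30% | 25% | 82% |
| 0.7 | 38% | 13% | 97% |

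Simulation (4,000 runs per setting) agrees: 20%, 31% and 37% for the arm test; 34%, 25% and 13% against 64%, 84% and 98% for arm-by-time. With a child term both tests stay near 5% under the null. With three visits instead of four, the pooled arm test still rejects a true null 15%, 22% and 29% of the time.

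**Reading 2: ANOVA at each visit.** There is one value per child, so the arm test keeps its size (about 5% in simulation) and has about 78–79% power at month 3 for 0.30 in both biscuit arms. It makes no use of baseline. An unpaired comparison of two visits within an arm has true size 2 × [1 − Φ(1.96 / √(1 − rho))] = 1.9%, 0.6% and 0.04%, so it is badly conservative.

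**Reading 3: repeated-measures ANOVA with baseline as one of four levels.** Error rates hold. The arm main effect averages in a visit before treatment: (0 + 3 × 0.30)/4 = 0.225. At rho 0.7 its power is about 66%, against about 98% for arm-by-time in the same simulated data, so it matters which term decides.

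**What baseline adjustment adds at one visit.** The residual SD is 0.95 × √(1 − rho²) = 0.906, 0.823 and 0.678. Pairwise power rises from 76% to 80%, 87% and 96%. The entry criteria, however, confine baseline to about one z unit. If baseline is uniform over that range, its SD is 1/√12 = 0.29. Correcting rho for this restriction (u = 0.29/0.95; rho·u / √[1 − rho² + rho²u²]) gives 0.10, 0.17 and 0.29. With the follow-up SD held at 0.95, power is then 77%, 78% and 80%.

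**The case against.** The strongest objection is that no wrong model is written down. A reader might infer that the plan is a plain ANOVA that treats four scores as four children, so that its arm test is far too liberal and its arm-by-time test far too weak. The documents do not support that as a statement of fact. A comparison between groups and between times describes a repeated-measures ANOVA equally well, and excluding children lost to follow-up leaves the complete sets of visits which that method needs. The sample size formula, with one value per child, points if anything to a comparison at a single visit. The article names neither a pooled arm effect nor an arm-by-time test, and the 0.30 was not set as an arm-by-time target. All of this stands, so the figures under reading 1 are conditional.

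Two further points also stand. The dilution to 0.225 comes from treating baseline as an outcome and would occur with a child term too. The error rates near 5% with a child term ignore allocation by sub-district, so they are not this trial's actual error rates.

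A further argument is that a condensed article may leave the type of ANOVA to a fuller document. That weakens the point but does not dispose of it. The article names a method, and each of its three plausible meanings has a drawback: one is invalid, one leaves an unpaired test over time and unused baseline data, and one dilutes the arm effect. Adding only the word repeated-measures would cure the first and leave the third.

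**Conclusion.** The point holds as a conditional one. The stated method is too unspecific for a four-visit outcome, and every reading can be improved at almost no cost. The harm is serious only if the scores are pooled: about 20–38% false positives for the arm test, and 13–36% rather than 64–98% power for arm-by-time, at rho 0.3–0.7. Under the other readings the loss is one of efficiency and clarity. The gain from baseline adjustment at a single visit lies between almost nothing (76% to 77%) and substantial (76% to 96%), depending on rho and on how far the entry range narrows baseline.

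All these figures rest on an assumed equal correlation, 144 children per arm and no clustering. This is a cheap improvement, not a demonstrated error in the plan.

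**What to change.** Replace the ANOVA sentence with wording such as: weight-for-length z-scores at months 3, 6 and 9 will be analysed in a linear mixed model for repeated measures (SPSS MIXED), with arm, visit and arm-by-visit as fixed effects, the child as repeated subject, and baseline z-score as a covariate and not as an outcome visit; the treatment effect is the between-arm contrast at a named visit. The visit should be named in the text.

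The child term should stand in addition to any term for the sub-district allocation described under Sampling method. Neither replaces the other: a sub-district term does not remove within-child correlation, and a child term does not handle clustering.

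The cost is slightly more analysis work. Any arm effect pooled over visits will have a wider interval than a plain ANOVA would show, because the plain interval is too narrow. No new data, visits or children are needed.

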**Method:**

The efficacy of a government food supplementation programme will be examined using a randomized control trial design. Parents with wasting children aged 6–17 months will be recruited to participate in the study. After obtaining informed consent and pre-intervention measures, participants will be assigned into three arms of intervention with PMT biscuits and/or nutrition education only. The two primary outcomes for this study are the nutritional status of wasting children and PMT biscuit compliance. Characteristics of all subjects in each arm will be analysed and compared with each other to assess their comparability at the beginning. The data will be collected at pre-intervention, at 3 months of intervention, post-intervention, and at the 6- to 9-month follow up.

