### Sampling method

The sampling procedure is started by selecting provinces and districts in cooperation with the Ministry of Health. Next, among sub-districts with a moderate prevalence of wasting children, three are selected to become arms of the study. The prevalence rate of moderate wasting is 10–15%, and the decision to include moderate wasting is to maintain the heterogeneity conditions of the selected sub-districts. Three selected sub-districts are then selected randomly to be assigned as arm 1 (control) and arms 2 and 3 (intervention 1 and 2, respectively). Subjects are generated from *posyandu*, from which only those with 2–5 eligible children were chosen. Thus, to fulfil the total number of 30 subjects, each sub-district involves 6–15 *posyandu*. Expansion to another sub-district will be done when there are fewer than 30 wasting children aged 6–17 months in each selected sub-district. The sampling method scheme is provided in Fig. 3.

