### Place and time of execution

Data collection will be conducted in 7 selected sites in Indonesia in accordance with Ministry of Health Coordination (Sambas Regency - West Borneo [1.3625° N, 109.2832° E], Depok Municipality – West Java [6°24′8.94″S, 106°47′39.27″E], Padang Pariaman Regency – West Sumatra[0.5547° S, 100.2152° E], Sleman Regency – Yogyakarta [7.7325° S, 110.4024° E], Banjar Baru Municipality – South Borneo [3°27′26.07″S, 114°48′37.14″E], Sidoarjo Regency – East Java [7.4726° S, 112.6675° E], Makassar Municipality – South Sulawesi [5°8′39.76″S, 119°25′35.9″E]). Data from each site are collected by investigators from 7 research centres of respected universities in Indonesia (SEAMEO RECFON, Faculty of Public Health Universitas Indonesia; Faculty of Public Health Andalas University; Faculty of Public Health Lambung Mangkurat University; Faculty of Medicine, Public Health, and Nursing Universitas Gadjah Mada; Faculty of Public Health Airlangga University; Faculty of Public Health Hasanuddin University). SEAMEO RECFON serves as a lead investigator. This study is planned for 3 months using a grant scheme in 2017 so that implementation in the 6th and 9th months will be continued in 2018. The enrolment of the study participants was initiated in January 2018 and finalized in April 2018. It is expected that the final data collection would be in December 2018.

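### Sub-districts are randomised but the ANOVA has no sub-district term, so standard errors are too small, by an amount that depends on an ICC the protocol does not give

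*Protocol article*

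**What the plan says.** The only operational account of allocation is in the Sampling method section of the protocol article. In each district, "three are selected to become arms of the study". Then: "Three selected sub-districts are then selected randomly to be assigned as arm 1 (control) and arms 2 and 3". Children are recruited from posyandu inside the chosen sub-district until there are 30, so all children of a sub-district receive the same arm. If too few are found, recruitment extends to another sub-district; the section does not say how that one is allocated.

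The Sample size section plans 30 children per arm in each district and concludes that "a minimum of 6 districts is needed to meet the minimum sample size required". Place and time of execution says: "Data collection will be conducted in 7 selected sites in Indonesia". There are therefore 6 or 7 sub-districts per arm.

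The abstract describes allocation differently. After consent and baseline measures, "participants will be assigned into three arms of intervention with PMT biscuits and/or nutrition education only". The Methods/design section presents an open-label, three-arm parallel trial and nowhere calls it cluster-randomised.

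For the analysis, the Plan of data analysis and presentation says: "The comparison of the weight-per-length score between groups and between times will be performed using ANOVA". It mentions no sub-district, posyandu or district term, no cluster-level summary and no robust standard error. The sample size comes from a comparison of two means, with no ICC or design effect.

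**The concern.** When whole sub-districts are allocated, the arm contrast is a contrast between sub-districts, and its variance includes the variation between them. An ANOVA with children as units leaves that part out. It treats 6 or 7 randomised units per arm as if they were 180 to 210 independently randomised children.

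The analysis sentence does not itself name the unit. The child-level reading follows from the individual-level sample size formula and from the absence of any cluster term.

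Some correlation is plausible from the text. Children come from local posyandu and are counselled monthly by health-centre nutritionists and cadres. What is at stake is the primary outcome, weight-for-length. If its p-values are too small and its intervals too narrow, the trial could report an effect of biscuits to the government on precision that the design does not provide.

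**Working it through.** **Inputs from the protocol.** SD 0.95, difference 0.30, 95% confidence (taken as two-sided), 80% power, 20% drop-out, 30 children per sub-district, 6 or 7 sub-districts per arm. After drop-out, 30 × 0.80 = 24 children per sub-district. The ICC is not given, so a range is assumed. It means the share of variance between sub-districts of the same district.

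**Step 1: the plan's own figure.** n = 2(1.96 + 0.84)² × 0.95² / 0.30² = 157.4, so 158 per arm. With drop-out, 158 / 0.80 = 197.5, so 198 per arm and 594 in total. The protocol states 540. A one-sided calculation gives 124, then 155 per arm and 465 in total. Neither reproduces 540. That is a separate matter; what counts here is that the formula has no clustering term.

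**Step 2: pairwise test.** The design effect is DE = 1 + (m − 1) × ICC. A child-level standard error is 1/√DE of the true one. The true size of a nominal 5% test is 2[1 − Φ(1.96/√DE)].

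**Step 3: three-arm F test.** One-way ANOVA on children at a single time point was simulated with no true arm effect (20,000 or more runs per setting).

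| ICC (assumed) | DE, m = 24 | Pairwise, m = 24 | F test, 7 × 24 | DE, m = 30 | Pairwise, m = 30 | F test, 6 × 30 |
|---|---|---|---|---|---|---|
| 0.005 | 1.115 | 6.3% | about 7% | 1.145 | 6.7% | about 7% |
| 0.01 | 1.23 | 7.7% | about 9% | 1.29 | 8.4% | about 10% |
| 0.02 | 1.46 | 10.5% | about 13% | 1.58 | 11.9% | about 15% |
| 0.05 | 2.15 | 18.1% | about 25% | 2.45 | 21.1% | about 29% |

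Example: at ICC 0.02 and m = 24, DE = 1 + 23 × 0.02 = 1.46, 1.96/√1.46 = 1.62, and the two-sided tail is 10.5%.

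**Step 4: does a cluster-level analysis cure it?** ANOVA of sub-district means on arm and district held between 4.6% and 5.4% in every setting. With k districts it has 3k − 1 − (k − 1) − 2 = 2(k − 1) residual degrees of freedom: 10 for 6 districts and 12 for 7.

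**Step 5: power of the cluster-level test.** With 7 × 24 = 168 children per arm, SE = 0.95 × √(2 × DE / 168). This is 0.115, 0.125 and 0.152 at ICC 0.01, 0.02 and 0.05. Dividing 0.30 by these gives noncentrality 2.61, 2.40 and 1.97. Against the noncentral t with 12 degrees of freedom (critical value 2.18), power is about 67%, 60% and 44%. At ICC 0 the same test would have about 76%, so part of the loss comes from the few degrees of freedom.

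**The case against.** **The size is assumed.** A reader might infer that the error rate is known to be well above 5%. The documents do not support that, because they give no ICC. At 0.002 the error is only about 6%. Entry is limited to a narrow weight-for-length band, and sub-districts to wasting prevalence of 10–15%. Both restrict baseline differences between sub-districts, though not necessarily differences in response. This stands.

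**Each district holds all three arms.** Effects shared by a district cancel from the arm contrast; only differences between its sub-districts matter. If district is left out of the ANOVA, its variance enlarges the residual and offsets a little of the inflation. With a district share of 0.05 and m = 24, the offset is complete only if the sub-district share is below 0.05/23 = 0.0022. Adding district as a factor removes the offset and does not cure the problem.

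**The check covers one time point.** The plan also compares times. In a group-by-time test a stable sub-district level cancels, and the relevant ICC is that of change, which may differ. This stands as a limit on the figures.

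**The causes of correlation.** A reader might add that children in a sub-district share a season, a food supply or one anthropometrist. The text does not say so; measurement training is organised by research centre.

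**Allocation may be individual.** The abstract can be read that way. The sampling section is more detailed and describes no procedure for randomising children, so it probably governs. The two must be reconciled.

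**An analysis plan may deal with it.** The point is not an omission: the article names a method and a sample size formula that do not match its own allocation.

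**Conclusion.** The mismatch is real and should be corrected before analysis. On the allocation described under Sampling method, a child-level ANOVA gives standard errors that are too small and a type I error above 5% for any positive sub-district ICC within districts. The only qualification is the slight offset when district is left unfitted.

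The direction is firm and the size is not. For a single-time comparison with 7 sub-districts of 24 children per arm, the F test runs from about 7% at ICC 0.005 to about 25% at 0.05, and a pairwise test from about 6% to 18%. These figures assume equal cluster sizes, no expansion sub-districts and the child-level reading of the ANOVA. The point would fall only if children were in fact randomised individually.

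**What to change.** 1. Reconcile the abstract with the Sampling method section, and state that the trial is cluster-randomised by sub-district within district.
2. Replace the ANOVA with a linear mixed model for weight-for-length: arm, time and their interaction, district as block, a random sub-district effect, the repeated measurements of each child, and small-sample degrees of freedom such as Satterthwaite. An alternative is an analysis of sub-district means on arm and district, with 10 to 12 residual degrees of freedom. The two are equivalent only when cluster sizes are equal, which losses and expansion would disturb.
3. State how expansion sub-districts are allocated. Count one as a separate cluster only if it is itself randomised; otherwise keep it within the randomised sub-district that it supplements.
4. Report the ICC, and restate the power in the Sample size section with an assumed ICC.

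No new data or extra enrolment is needed. A reader might infer that the change is one of wording only, but it has a statistical cost: confidence intervals widen, and the claimed 80% power must be replaced by a lower figure, as in step 5 of the working.

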### Data monitoring committee

A committee to monitor data collection has been established and comprises an advisory board of experts at SEAMEO RECFON. The data monitoring committee (DMC) is not involved in the study as a team member. The DMC advises the study team members regarding the continuing safety of trial subjects as well as the continuing validity and scientific merit of the trial.

## Discussion

Food supplementation in the form of a biscuit has been established for a decade as a national programme to reduce wasting prevalence in Indonesia. The official daily serving size of the biscuit is considered very dense in energy and another macronutrients. Unfortunately, information on its effectiveness is lacking, and the concern of the energy dense nature provided might inhibit another nutrient. The decision of food supplementation in the form of biscuits and the serving needed to be consumed daily have not been supported experimental study-based evidence in the community. There is a concern that if the amount of biscuit given is too energy dense, it may inhibit the absorption of other nutrients. This study intends to examine the effectiveness of consuming supplementary biscuits and provide alternative strategies that can achieve optimal results. Additionally, an alternative strategy is proposed in this study by modifying the daily serving size and highlighting the use of local based food in a nutrition education session.

